### Proposed intervention

Globally, Indigenous notions of health and illness are generally defined more broadly than a Western biomedical definition that focuses more often on physical health or the absence of disease [22]. In Australia, the National Aboriginal Health Strategy, [[23], p.x] defines Indigenous 'health' holistically as the physical, social, emotional, and cultural wellbeing of the individual and the community. In NZ, Te Whare Tapa Wha, a widely used Māori model of health is based on the four-sided whareuni or meeting house. It incorporates tinana (physical body), hinengaro (psychological), whānau (family and community), and wairua (spirit) [20]. Balance between these dimensions is required in order to maintain stability and good health. Poor health develops when there is a breakdown in the harmony of these four realms within the individual or in their relationship to the wider environment [20].

In this study, the intervention program about ETS will be framed around an Indigenous model of health promotion, which attends to the psychological, physical, spiritual and cultural wellbeing of the individual and the family/community, as it relates to this project. In NZ, Te Whare Tapa Wha will be used. This model has been applied to understanding Māori smoking cessation behaviour [20] and for guiding the development of culturally appropriate smoking cessation programs and strategies [24]. In Australia, the model will draw on similar concepts. The counselling/psychological component of the intervention program is founded on social cognitive theory and motivational interviewing.

Participants will be told that they will be randomly assigned to a group that receives 'usual care', or a group that receives extra home visits by an IHW, and that a variety of study measurements will be taken over a 12-month period.

• **Treatment group: **The intervention program will (i) provide information and education about the health effects of ETS exposure and use behavioural 'coaching' techniques to help mothers/caregivers and family members implement strategies to reduce the infant's ETS exposure, as well as (ii) identify the smokers among other household members and deliver culturally appropriate smoking cessation advice, counselling and treatment options as requested. An eight weeks supply of free nicotine replacement therapy (NRT) (patches or gum) will be available to participants and other household members for whom such drug therapy is indicated (i.e. they are motivated to quit, are nicotine dependent and have no contraindications to taking NRT). NRT will be provided by the IHW with appropriate counselling and follow-up. Furthermore, for those that are interested a fax referral to Quitline will be offered, with proactive call back by Quitline.

The intervention program will be delivered during three face-to-face home visits (of approximately 45-60 minutes) conducted over the first three months of the infant's life. Culturally appropriate resources (e.g. flip charts, 'No Smoking' stickers, posters, etc) will be used to assist in both education and behavioural 'coaching'. These resources will be obtained from relevant health groups in each country who hold a repository of such resources (e.g. QUIT Victoria, the Northern Territory Department of Health and Families, Auckland Regional Public Health Service). IHWs will deliver the program after appropriate training, and will complete standardised progress reports after each program session, which will be used at a weekly team meeting with the health workers and study personnel for discussion and ongoing training.

• **Control group: **The control group will receive 'usual' care through their community health provider. Usual care entails routine visits to maternal and child health providers at several defined time points during the first 12 months of the infant's life. At these postnatal visits, health providers check developmental milestones and general wellbeing. Additionally, mothers/caregivers routinely receive messages about smoking cessation and ETS exposure in their homes during these visits as part of general health promotion.

In addition to the above, the IHWs will briefly check that both groups have received the 'usual' care delivered to new mothers and their infants through routine 'well baby' visits in the first 12 months of life through their standard health provider (i.e. the study team will check these infants are not 'falling through the gaps' in the health system). This will be undertaken at baseline, when the infant is four months and one year of age. The focus will be on key health promotion messages that should have been delivered at routine community health visits (e.g. immunisations, infant nutrition/breastfeeding and safe sleeping for baby.) Mothers/caregivers will be given a few key messages if they have not received this information, e.g. clear face, sleep on back for SIDS prevention. If these visits have not been attended or if the key messages have not been received by the mothers/caregivers, they will be referred back to their usual maternal and child health provider.

### Outcome measures

Primary Outcome: *Rate of health provider presentations for new primary episodes of ARI in the first year of life*.

All participating infants will be evaluated at baseline and when the infant is four and 12 months old, for the occurrence of medically attended acute respiratory illnesses (MAARI). These are defined as new onset events, including a change from the child's baseline medical status, referable to the upper and/or lower respiratory tracts. To identify episodes of ARI mothers/caregivers will be asked at baseline, and when the infant is four and 12 months old, whether their child has had any presentation to the clinic or hospital and the names of the clinics attended. Research assistants will collect the source data relevant to the primary outcome measures, so will review the individual child's health provider and hospital clinic records (parental consent will be obtained prior to accessing records). Source documents will be photocopied, de-identified, labeled with the participant registration, and stored with the trial records. Two clinicians at each study centre will review the records and confirm documented respiratory illnesses without knowing the group allocation of the individual children. MAARI events will be evaluated by these clinicians to determine whether they are medically-attended upper respiratory infection (URI), lower respiratory infection (LRI) and/or otitis media infection (based on the definitions in Additional file 1: Table S1). Conflict will be resolved by discussion and consensus between the two clinicians. Intra-rater and inter-country reliability testing will be performed on primary outcome data from 20 participants at each site. Information on antibiotic use for the treatment of medically attended URI, LRI or otitis media events will not be collected.

Major secondary outcomes:

▪ *Rate of hospitalizations for ARI*: same case definition as primary outcome measure.

▪ *Urinary cotinine*: Urinary cotinine, a metabolite of nicotine, is recommended as the best biomarker [25]. It has a relatively long half-life (32-82 hours in children) [26]. The laboratory will use gas chromatography/mass spectrometry (GCMS) in selected-ion-monitoring mode with a stable isotope internal standard. This method provides a sensitive analytical method with high specificity [27]. Urine samples from infants will be obtained by placing several sterile cotton balls in a clean nappy. The wet cotton balls will subsequently be packed into a sterile 20 mL syringe (without needle) and the urine expressed into a 10 mL sterile specimen jar which will be delivered to the contracted medical laboratory in each country for analysis. Urinary creatinine will be measured concurrently and results expressed as the cotinine/creatinine ratio (ng/mg).

Minor secondary outcomes and likely mediators of effect:

▪ *Mother/caregiver's self-report of infant's exposure to ETS: *Number of days in the preceding seven days in which infant was exposed to ETS (same room in a house with a person who smokes, in a car with a person who smokes, or sitting outside within arm's length of someone who smokes).

▪ *Mother/caregiver's self-report of smoking restrictions in the home and car*.

▪ *Mother/caregiver's self-report of smoking cessation*: defined as mother/caregiver not smoking a single cigarette (not even a puff), in the preceding seven days. We will also be assessing prolonged abstinence (e.g. quit for 3 months at 4 month follow up; quit for 9 months at 12 month follow-up).

▪ *Mother/caregiver's self-report of number quit attempts*: defined as not smoking a cigarette for at least 24 hours.

▪ *Process evaluation indicators*: a mix of quantitative and qualitative measures to assess how well the intervention program was implemented according to protocol e.g. number of 'coaching' activities completed, obstacles and successes in delivering program, parent satisfaction with the program.

### Sample size

A total sample size of 190 provides 90% power (5% significance) to detect a 25% reduction of new episodes of respiratory illness (primary outcome) in the intervention group compared to the control group. This is based on a conservative estimate of an average of 3 health provider visits per year in the control group, compared to an average of 2.25 visits in the intervention group (assuming a Poisson distribution where the mean equals the variance). There are few published data on the community burden of ARIs in Northern Territory Indigenous children or NZ Māori children. In a recent study of disease burden and clinic attendances for young Indigenous children in two remote Northern Territory communities, the median number of presentations for upper respiratory illness in the first year of life was 7.5 (interquartile range 4-11) and for lower respiratory illness, 2.5 (interquartile range 1-5) [28]. The overall number of episodes of respiratory illness is likely to be less in an urban setting compared to that in the remote contexts [29]. Thus, it is estimated that an average of 3 visits per year be undertaken in the control group for the sample size calculation above. A maximum of 10% loss to follow-up is expected, as there are multiple contact points throughout the study for both groups and because the primary outcome (rate of respiratory infections) even in children who leave the study region before 12 months of age can be measured. Thus, 210 children in each country will be recruited. Given that there are limited data to base the likely effect size on, it is possible that the effect size chosen may be optimistic. By combining data from NZ and Australia the sample size is increased to 380 participants (420 if loss to follow-up is factored in), which will provide 90% power (at 5% significance level) to detect an 18% reduction in new episodes of ARI in the intervention group compared to the control group.

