#### Treatment effects

Analysis of the primary outcome will involve comparing the rate of respiratory illness between the two groups. Simple unadjusted rates, relative risks and 95% confidence intervals will be obtained in the first instance, with subsequent multiple regression analysis adjusting for other variables. Two forms of regression analysis will be considered for the primary outcome: poisson regression analysis and negative binomial if there is evidence of overdispersion or underdispersion. Analysis of secondary outcomes will be conducted using standard statistical procedures applicable to categorical or continuous data. A per-protocol analysis will also be performed in order to check the robustness of the results. All tests of significance will be two-tailed.

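### The 90% power figures assume Poisson counts, although the infant data cited beside them are clearly overdispersed; with similar dispersion at the planned rate, power would be roughly 48-73%

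*Protocol article*

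**What the plan says.** The Sample size section of the protocol article opens with the per-country claim: "A total sample size of 190 provides 90% power (5% significance") for a 25% reduction. The rates behind it are "an average of 3 health provider visits per year in the control group, compared to an average of 2.25 visits in the intervention group", and the variance rule is "assuming a Poisson distribution where the mean equals the variance".

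For the two countries pooled, the evaluable total is 380, with 420 to be recruited. The power claim attached to that total reads: "which will provide 90% power (at 5% significance level) to detect an 18% reduction in new episodes of ARI". No other variance allowance is mentioned for the pooled figure.

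To support the control rate, the section cites a study of two remote Northern Territory communities, where "the median number of presentations for upper respiratory illness in the first year of life was 7.5 (interquartile range 4-11"). For lower respiratory illness it gives a median of 2.5 and quartiles of 1 and 5. These data are used only to argue that a mean of 3 is conservative for an urban setting. Their spread is not discussed.

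Under Treatment effects, the primary outcome is to be analysed by Poisson regression, or "negative binomial if there is evidence of overdispersion or underdispersion". The same section states: "All tests of significance will be two-tailed".

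**The concern.** For counts of repeated illness, the power of a rate comparison depends on how much infants differ in their underlying rates as well as on the mean. Setting the variance equal to the mean assumes that they do not differ at all within an arm. The only dispersion information in the protocol points the other way, and the analysis section allows for overdispersion where the sample size does not.

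What is at stake is how the result is read. The recruitment target of 210 per country rests on the first 90% figure, and Data Analyses commits to analysing each country separately as well as combined. A null result, particularly within one country, would be judged against a power that the design may well not have.

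**Working it through.** **Inputs.** From Sample size: control mean 3; intervention mean 2.25 (25% reduction) or 3 × 0.82 = 2.46 (18% reduction); 95 or 190 evaluable infants per arm; 5% significance. From Treatment effects: two-sided tests. Assumed: about one infant-year of follow-up each.

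**Step 1: reproduce the stated figures.** With n per arm, Var(ln RR) = (1/m1 + 1/m2)/n and power = Φ(|ln RR|/SE − 1.96).
- 190 infants, 25%: SE = √((1/3 + 1/2.25)/95) = 0.0905; 0.2877/0.0905 = 3.18; power 88.9%.
- 380 infants, 18%: SE = √((1/3 + 1/2.46)/190) = 0.0624; 0.1985/0.0624 = 3.18; power 88.9%.

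Both agree with 90% to rounding, so the arithmetic is sound and the pooled figure evidently uses the same Poisson variance.

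**Step 2: compare the cited data with a Poisson.** A Poisson with mean 7.5 has quartiles 6 and 9. For Poisson means from 6 to 10 the interquartile width is never more than 5; the cited width is 11 − 4 = 7. The lower-illness quartiles (1 and 5) are weaker evidence, because a Poisson with mean 3.4 has quartiles 2 and 5. The upper-illness data carry the argument.

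**Step 3: translate the spread into k**, with variance = mean + k × mean².
- Upper illness, by moments: SD ≈ 7/1.349 = 5.19, variance 26.9, k ≈ (26.9 − 7.5)/7.5² = 0.345. A negative binomial fitted to the three quartiles gives k ≈ 0.34 (mean about 8.3).
- Lower illness, by quartile fit: k ≈ 0.66 (mean about 3.4). The moment formula gives about 1.0, but it puts a normal-theory SD and a median into a short, skewed count, so it is not relied on.
- Upper plus lower combined: the correlation is not given. Taking it from 0 to 1, with an assumed combined mean of 10 to 10.5, the variance is 35.7 to 66.5 and k ≈ 0.23 to 0.56.

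A working range of k = 0.2 to 0.65 covers these to within rounding.

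**Step 4: recompute power** with Var(ln RR) = (1/m1 + 1/m2 + 2k)/n. Example at k = 0.345, 190 infants, 25%: SE = √((0.778 + 0.690)/95) = 0.1243; 0.2877/0.1243 = 2.31; power 64%.

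| k | 190 infants, 25% | 380 infants, 18% | 380 infants, 25% |
|---|---|---|---|
| 0 | 89% | 89% | 99% |
| 0.2 | 73% | 73% | 95% |
| 0.345 | 64% | 63% | 91% |
| 0.5 | 56% | 55% | 84% |
| 0.65 | 49% | 48% | 79% |

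**Step 5: minimum detectable reduction at 90% power, control mean 3.** With 380 infants: 22% (k = 0.2), 25% (k = 0.345), 29% (k = 0.65). With 190 infants: 31%, 34% and 39%.

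**Step 6: a higher control mean.** For 190 infants and a 25% reduction, a mean of 5 gives 83% at k = 0.23 and 74% at k = 0.345. A mean of 10 gives 92% and 83%.

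**The case against.** The strongest reply is that the calculation is right for the assumption it declares, and that the contrary evidence is indirect. The cited infants lived in remote communities. Their counts are presentations, split into upper and lower illness, whereas the primary outcome is new episodes of either kind in urban infants. Repeat visits within one episode could inflate the spread of presentations relative to episodes. The protocol gives no urban dispersion, and the cited study is not to hand. This stands, and it is why the result is a conditional range.

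Second, the mean of 3 is deliberately conservative. The offset is real but partial: among the cases in Step 6, only a rate close to the remote one combined with low dispersion brings 190 infants back to 90%.

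Third, the negative binomial fallback and the confidence intervals protect the analysis, and the planned covariate adjustment may remove some between-infant variation. This too stands, but a correct error rate and an honest interval do not supply the stated power.

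A reader might go further and infer that the trial as a whole has only an even chance of finding its target effect. The documents do not support that. Figures near 50% arise only at the upper end of the k range and only for each size paired with its own stated effect. For the 25% reduction from which the planning starts, the pooled 380 keep about 79-91% power at k = 0.345 to 0.65. Nor is this an arithmetic error: the stated figures reproduce to rounding.

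**Conclusion.** The point holds in conditional form. The two 90% figures depend on variance equal to mean, and the only dispersion data in the protocol contradict that assumption. If relative heterogeneity like that of the cited remote infants applies to the combined urban outcome at a control mean of 3 (k about 0.2 to 0.65), power is roughly 48-73% for 190 infants at 25% and for 380 infants at 18%. At that mean, no dispersion within this range gives 90% for either claim. The conclusion rests on carrying k over from remote presentations, on a negative binomial variance, and on the planning mean of 3. The exact power is uncertain; that it is overstated for the planned rate is well supported. The per-country claim is the more exposed, since the pooled trial retains reasonable power for a 25% reduction.

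**What to change.** In the Sample size section, and in the statistical analysis plan if it repeats these figures:
- Restate power under a negative binomial variance, mean + k × mean², over a declared range such as k = 0.2 to 0.65. Label the range as an assumption carried over from the remote data.
- Give the minimum detectable reduction at 90% power: about 22-29% with 380 evaluable infants and 31-39% with 190.
- Withdraw the 90% claims for a 25% reduction within each country and for an 18% reduction pooled.

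This is a rewording. Enrolment need not change, and the planned analysis already allows for the negative binomial model. The only cost is a less favourable stated power.

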### Recruitment strategies

In Australia and NZ, mothers/caregivers will be approached for recruitment into the study through a range of community, Indigenous-controlled health and government hospital services. We will approach both pregnant women and new mothers to ascertain their interest in participating in the trial. If pregnant women are interested in the study, we will re-approach them after they have given birth. Eligible and interested mothers will be asked for their consent for randomization. Documented written consent will be obtained from all participants prior to entering the study. A range of project-specific advertising material will be produced (e.g. clinic posters, brochures) and local Indigenous media may be used to bolster recruitment.

### Planned recruitment rate and risk of loss to follow up

In 2006, there were approximately 240 Indigenous infants born to mothers who were resident in Darwin, Australia. We anticipate that 90% or 216 Indigenous infants/mothers will be eligible for recruitment annually into this study. In a separate study based in Darwin to improve ear health outcomes, 55% of Indigenous women approached in pregnancy have consented to participate in a randomized controlled vaccine study (pers. comm., [name] [Menzies School of Health Research], 10 January 2008). Using these figures, we could confidently anticipate that approximately 108 eligible Indigenous mothers will agree to participate in our study each year, or 9 per month. This is likely to be an underestimation, as our proposed study is less invasive than the ongoing vaccine trial (which requires immunisation and repeated blood samples).

It is anticipated that recruitment will be faster at the Auckland site owing to a larger eligible population. Approximately 580 babies are born each month at Middlemore Hospital, of which 21% are Māori [pers. comm., [name], Counties Manukau District Health Board]. Data reported in 2003 showed that about 55% of Māori pregnant women in NZ were smoking at the time of conception, and 15% of these women quit smoking during their pregnancy[30] From these data we can estimate that at least 57 Māori new mothers that smoke will be available per month to approach about the trial (mothers that are non-smokers but live in households with other smokers are also eligible). We anticipate that 90% or 51 infants (assuming no twins) will meet the inclusion criteria. We estimate that about 60% of women approached will agree to participate (i.e. 31 per month). Consequently it is expected to take about seven months to recruit the 210 people required for the NZ arm of the trial.

Figure 2 outlines the timeline for this study at both sites.

**Figure 2 F2:**
[figure not shown]
**Timeline for a randomized controlled trial of a family tobacco control program about ETS to reduce respiratory illness in Indigenous infants**.

### Withdrawal criteria

Participants may be withdrawn from the study if one or more of the following occurs:

• Voluntary withdrawal: A parent or primary caregiver can voluntarily withdraw their infant from the project at any time without having to provide a reason for doing so.

• Failure to meet eligibility criteria: An infant will be withdrawn from the project if their mother/caregiver has previously signed a consent form but they do not meet all the eligibility criteria at the baseline visit (when the infant is five weeks old +/- one week).

• Failure to be located after multiple follow-up home visits

• Death of infant

• Significant illness requiring prolonged hospitalization

• A serious and irreconcilable protocol violation (as determined by the Investigators)

In the event that a study participant dies, their family contact will be asked if they require the information recorded to be disposed of as per other participants at the completion of the study, or whether they wish the information to be returned to the family.

### Data Management

The design and management of all databases associated with this trial will be undertaken by the data management and information technology groups at the Clinical Trials Research Unit (CTRU), University of Auckland. The databases will be constructed in Oracle. Validation rules for each Case Report Form (CRF) will be specified by the site study managers, in association with the CTRU data manager. These rules will include range checks so that inaccuracies in data collection can be identified early. A query will be raised as soon as any values are entered that are outside the allowed range or if data are missing. The research assistants at each site will amend the CRF's as soon as a query is raised. All information collected from participants will be treated as strictly confidential. De-identified data will be stored in computers under a password secure file. Paper records will be stored under numerical code in a locked filing cabinet within a secure office area, and will only be accesses by approved study staff.

